### Hypothesis

The primary hypotheses are that compared to controls, the intervention group will spend more time (minutes per day) on moderate-to-vigorous intensity physical activity (MVPA) immediately post-intervention and at the 6 month follow-up. Secondary hypotheses are that the intervention group will spend more time on active transportation (cycling or walking), that the intervention effect will be larger among those who at baseline perceive their neighbourhood walkability as low and that attitudes towards active transport will improve more compared to the controls. We further hypothesize that the intervention group will report improved health related quality of life at the end of the intervention and at the 6 month follow-up.

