#### Health related quality of life

Health related quality of life will be assessed using the commonly used RAND-36 questionnaire [38, 39]. The RAND-36 consists of 36 items and measures of perceived health across eight domains using a 0–100 scale: 1) physical functioning; 2) bodily pain; 3) role limitations caused by physical health problems; 4) role limitations caused by emotional problems; 5) general mental health; 6) social functioning; 7) energy/fatigue and (8) general health [40].

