#### Sociodemographic factors

At baseline, participants will complete questions regarding sociodemographic data e.g., sex, age, country of birth, educational attainment, weight and height, and family structure. At follow-up only questions that may have changed and are of relevance for the purpose of the study are repeated, such as if the participant has moved, occupational status or if the participant has access to a bike.

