### Statistical analyses

Trial evaluation will be performed with linear mixed model analyses using intention to treat principles. In the statistical models we will use time as a categorical variable (0, 3 and 6 months) with time 0 as a reference group and include an interaction between group and time. The dependent variable is post intervention scores for MVPA (i.e., minutes/day) and the secondary outcomes (e.g., active transportation (minutes/day)). Three-way interactions will be analysed in order to evaluate if the intervention effect was moderated by any of the baseline covariates (e.g., age, sex, educational attainment, neighbourhood walkability or health related quality of life). Missing values on baseline covariates and on follow-up assessments will be imputed simultaneously using multiple imputation with chained equations [m (number of imputations) = 20] [44] taking into account variables of importance for predicting the missing values (e.g., age, sex, country of birth, educational attainment, occupation, season for intervention (i.e., autumn or spring) etc.). Continuous variables will be imputed using predictive mean matching (5 nearest neighbours). Binary variables will be imputed using logistic regression, and multi-categorical variables will be imputed using ordinal logistic regression (if ordered) or multinomial logistic regression (if unordered). Descriptive data over adherence to the intervention will be presented. Per protocol analyses examining effects related to adherence to the intervention (e.g., number of registered days in the app, goals set and achieved) will be conducted using linear mixed models adjusting for age, sex, country of birth (Sweden/not Sweden), educational attainment, occupation and season for intervention. As in the primary analysis, time, group and time-group-interactions will also be included. Sensitivity analyses concerning deviations from the missing at random assumption will be performed using delta-adjustment [45]. Statistics Sweden will provide summary statistics for responders and non-responders regarding age, sex, country of birth, education level and area of residence. All *p*-values < 0.05 (two-sided) will be regarded as statistically significant.

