We chose to recruit our population from a random sample of the general population, using letters sent out by Statistic Sweden, which we have successfully used previously [32, 54]. We believe that we thereby obtain a heterogeneous sampling frame of participants, enabling us to examine the intervention effect among participants with various characteristics. It is possible that this study attracts those who are already physically active and thus the intervention effect may be reduced. However, with the chosen design we have the opportunity to reach a large sample and to test the usability of the app in an appropriate manner before extending the use of the app to other populations. In the future, possible arenas for implementation of the app are municipalities wanting to improve public health in the general population. Thus, we are evaluating the app in the same context as it will be delivered.

Active transportation is cheap, easy-to-use and can become a daily habit for many people. Thus, if the TRavelVU Plus app is effective it has potential to offer a low-cost intervention that can be delivered at scale to promote active transportation. Active transportation can significantly contribute to increasing physical activity levels and thus improve the health of many and thereby decrease related societal health care costs.

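### Moderation is tested on an open list of baseline covariates with every p-value below 0.05 called significant: about an 18–23% chance of a false moderator at 3 months from the five named covariates

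*Protocol article*

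**What the plan says.** Four places in the protocol article bear on this.

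- **Statistical analyses, moderation:** "Three-way interactions will be analysed in order to evaluate if the intervention effect was moderated by any of the baseline covariates". The covariates follow in brackets as examples: "e.g., age, sex, educational attainment, neighbourhood walkability or health related quality of life". Time is categorical (0, 3 and 6 months, with 0 as reference), so each moderator brings a 3-month and a 6-month interaction term.
- **Statistical analyses, last sentence:** the threshold is set for all p-values in the trial: "values < 0.05 (two-sided) will be regarded as statistically significant".
- **Hypothesis:** one moderation hypothesis is stated, with a direction: "the intervention effect will be larger among those who at baseline perceive their neighbourhood walkability as low".
- **Outcomes and measures:** the primary outcome is MVPA at 3 months after randomisation.

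Two further sections show how the list could grow. The sociodemographic baseline data are themselves given as examples ("e.g., sex, age, country of birth, educational attainment, weight and height, and family structure"), and RAND-36 yields "measures of perceived health across eight domains using a 0–100 scale".

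**The concern.** The article has one moderator with a stated rationale and direction, but its decision rule treats that moderator like any other baseline covariate. Walkability appears fourth among five examples. An unforeseen interaction with age, sex, education or quality of life would be called significant on the same terms as the hypothesised one.

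At stake is what the trial may say about who benefits. The authors want to look at this: the sample size section mentions subgroup analyses when justifying the number of people approached, and the Discussion presents the sampling frame as "enabling us to examine the intervention effect among participants with various characteristics". If the effect does not vary between people, a report that follows the written rule would still announce a significant moderator far more often than a reader of a 0.05 threshold would expect.

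**Working it through.** **The plan's own figure.** The only design calculation is the sample size for the main effect (difference 10 min/day, SD 25, two-sided 0.05, 80% power).

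- n per arm = 2 × (1.960 + 0.842)² × 25² / 10² = 98.1, so 99.
- Power with 100 per arm: 10 / (25 × √(2/100)) = 2.83, and Φ(2.83 − 1.96) = 80.7%.
- Enrolment: 200 / (1 − 0.20) = 250.

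This reproduces. The article gives no error rate for the moderation tests, so that has to be derived.

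**Inputs.** From the article: five named moderators, two-sided 0.05 each, two post-baseline visits, 100 completers per arm. Assumed: no true moderation, one outcome, one quality-of-life score, correlation between moderators of 0 to 0.5, and correlation between the 3- and 6-month test statistics of 0.5 to 0.7.

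**At 3 months only.** For k independent tests the chance of at least one false positive is 1 − 0.95^k.

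- k = 5, independent: 1 − 0.95⁵ = 22.6%.
- k = 5, moderators correlated 0.2: 21.7%; correlated 0.5: 18.4%.
- Simulated trial (100 per arm, SD 25, moderators correlated 0.2, constant treatment effect, interaction tested on change from baseline, 4,000 replicates): 21.8%.

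The range is therefore about 18–23%.

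**Over both visits.** The answer depends on how the three-way term is tested, which the article does not say.

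- *One joint 2-df test per moderator:* again 1 − 0.95⁵ = 22.6% if independent; 23.1% in the simulated trial.
- *Separate 3- and 6-month tests:* for one moderator, the chance that at least one of two |Z| exceeds 1.96 is 9.1% at between-visit correlation 0.5 and 8.35% at 0.7. For five independent moderators this gives 1 − (1 − 0.0907)⁵, about 38%, and 1 − (1 − 0.0835)⁵ = 35%. With moderators correlated 0.5 and visits correlated 0.7 it is 28.8%. The simulated trial gave 37.1%. The range is about 29–38%.

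**If the list grows (assumptions, one outcome).**

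| Moderators tested | 3 months | Both visits, separate tests |
|---|---|---|
| Ten, independent | 1 − 0.95¹⁰ = 40.1% | 58–61% |
| Ten, correlated 0.5 | 29% | 44–47% |
| Four, plus eight RAND-36 domains correlated 0.5 | 37–40% | 58–62% |

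A joint test per moderator with ten moderators gives about 40% over both visits. A second outcome would raise the figures again.

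**The walkability hypothesis by itself.** It has a direction, so only a result in that direction supports it: 0.05 / 2 = 2.5% per test. Over two visits correlated 0.5, the two-sided chance of 9.07% implies that both tests exceed the threshold together with probability 0.100 − 0.0907 = 0.0093, almost all of it with the same sign. The one-sided chance is therefore 0.050 − 0.0093/2 = 4.5% (4.9% at correlation 0; 3.5% at 0.9).

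**After the fix.** One confirmatory test at one visit has a false-positive rate of 5.0% two-sided, 2.5% in the hypothesised direction.

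**The case against.** The best reply is that this is a condensed article. A closed list of moderators, the scoring of quality of life, joint or separate tests, and multiplicity for secondary analyses are all things an analysis plan normally settles, and that plan is not shown. The closing sentence on p-values may be no more than a routine threshold statement, and the article never claims family-wise control. This stands as far as it goes: the open list alone would not be a finding. But the article does more than stay silent. It extends moderation to any baseline covariate and applies the threshold to all p-values without exception, so a plan that held these tests to a different standard would have to depart from that sentence.

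Four stronger readings are tempting, and the article does not support them.

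- *That the false-moderator risk is 40% or 60%.* Those levels need about ten moderators or a split of RAND-36 into eight, and the higher one also needs separate visit tests. Quality of life is named once in the moderation sentence, and no number of moderators is fixed.
- *That the walkability hypothesis is too easily confirmed, at about 9% over two visits.* That counts significant results in the wrong direction. The figure for the hypothesis as stated is about 4.5%.
- *That roll-out will be decided on subgroup results.* The Discussion names municipalities seeking better health in the general population, and its remark about people in greatest need follows from a general argument about inactivity. Neither depends on a moderator.
- *That nothing indicates which outcome and visit should decide.* The article does fix MVPA at 3 months as primary, although it does not tie the moderation hypothesis to it.

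**Conclusion.** The concern holds in a limited form and is minor. Followed as written, the rule gives about an 18–23% chance of at least one false moderator at 3 months. Over both visits it is about 23% with joint tests or 29–38% with separate ones. These figures rest on the five named moderators, one outcome, no true moderation, and the correlations stated above. More moderators, RAND-36 domains or outcomes would raise them, but by how much cannot be read from the article.

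The inflation concerns claims about moderators other than walkability. A reader might infer that the trial's main result is compromised; it is not, because the primary MVPA comparison at 3 months does not depend on these tests.

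**What to change.** In Statistical analyses:

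1. Name group × time × walkability index, for MVPA at 3 months, as the single confirmatory moderation test at two-sided 0.05. This matches the one stated hypothesis and the primary outcome and visit.
2. Label all other three-way interactions exploratory: the other moderators, the 6-month terms and the secondary outcomes. Report them with estimates and 95% confidence intervals.
3. Exempt those exploratory tests from the sentence that calls all p-values below 0.05 significant.

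The change is wording only, with no new data or participants and no effect on the primary analysis. The cost is that moderators other than walkability can no longer be declared significant.

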## Methods

### Study design

SCAMPI is a two-arm parallel randomised controlled trial (RCT) (1:1 ratio) conducted in Stockholm County, Sweden, with assessments at baseline, post intervention at 3 months and 6 months post randomisation (see Fig. 1 for study outline). This study protocol follows the SPIRIT 2013 statement [21, 22] and the intervention is described according to the CONSORT – EHEALTH checklist [23].

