### Trial status

In June 2017, final modifications to TRavelVU Plus were made and in August 2017 the app content and usability was tested in a pilot study, with minor changes to the app being made thereafter. Recruitment of participants, baseline assessments and randomisation of participants started in September 2017 and will continue until April 2018. Outcome assessments at the end of the intervention will be finalised by July 2018. Follow-up assessments (six months after randomisation) will be finalised in October 2018.

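### In the per-protocol model, one autumn/spring label per person entered as a main effect cannot adjust change from baseline for season

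*Protocol article*

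**What the plan says.** The Statistical analyses section uses season in two places.

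- **Multiple imputation.** The models are built "taking into account variables of importance for predicting the missing values". Among the examples is "season for intervention (i.e., autumn or spring", which is where the two levels are given. The list is open-ended.
- **Per-protocol mixed model.** This examines effects related to adherence (days registered in the app, goals set and achieved). Its covariates end with "educational attainment, occupation and season for intervention". Beyond the covariates, only time, group and their interaction are stated.

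Season is not listed for the primary intention-to-treat model.

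On the calendar, Study design sets "assessments at baseline, post intervention at 3 months and 6 months post randomisation". Trial status says "randomisation of participants started in September 2017 and will continue until April 2018", then "Outcome assessments at the end of the intervention will be finalised by July 2018" and "Follow-up assessments (six months after randomisation) will be finalised in October 2018".

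**The concern.** Walking and cycling outdoors plausibly vary with the time of year, and the plan itself treats season as worth adjusting for. The variable it names has one value per person, while the season of measurement changes from visit to visit. A model with time as a categorical factor and a group-by-time interaction estimates differences in change from baseline. A covariate that is constant within a person and has no interaction with time adds the same amount at every visit, so it drops out of that change.

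This matters most in the per-protocol analysis. Its comparisons depend on adherence, which is observed after randomisation and not allocated by it. Reaching a walking or cycling goal may depend on the time of year, as may moderate-to-vigorous physical activity (MVPA). If so, season is a confounder there, and the stated adjustment does little about it.

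**Working it through.** **Plan's own figures.** The plan gives no figure for season. Its sample size reproduces and is not affected: 2 × (1.96 + 0.84)² × 25² / 10² ≈ 98–99 per arm against 100 stated, and 200 / 0.80 = 250.

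**Step 1: calendar.** Inputs are start months September to April (Trial status) and visits at +0, +3 and +6 months (Study design). With three-month calendar seasons and winter as December–February:

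| Start | Baseline | 3 months | 6 months |
|---|---|---|---|
| Sep–Nov | autumn | winter (Dec–Feb) | spring (Mar–May) |
| Dec–Feb | winter | spring (Mar–May) | summer (Jun–Aug) |
| Mar–Apr | spring | summer (Jun–Jul) | autumn (Sep–Oct) |

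The last row ends in July and October 2018, which matches Trial status. Every start month gives three different seasons. Three of the eight start months are winter months.

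**Step 2: what a main effect can do.** Assume a seasonal term A·cos(2π(month − peak)/12), even entry over the eight months, and a two-level label split at some point in the window. The documents give neither the curve nor the amplitude A. Let s₀, s₃ and s₆ be the difference in the seasonal term between later and earlier starters at each visit, in units of A. Baseline and 6 months are half a year apart, and cos(x + π) = −cos(x), so s₆ = −s₀. The single fitted slope is therefore b = (s₀ + s₃ + s₆)/3 = s₃/3.

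*Example: July peak, split December/January.* s₀ = −0.38, s₃ = 1.40, s₆ = 0.38, so b = 1.40/3 = 0.467. Eight start months at three visits, each 0.5 from the label mean, give a label sum of squares of 24 × 0.25 = 6. The seasonal sums of squares within visits are 1.94 + 4.66 + 1.94 = 8.54. Share captured: 0.467² × 6 / 8.54 = 1.31 / 8.54 = 15%.

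**Step 3: across peaks (split December/January).**

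| Peak | s₀, s₃, s₆ | Label, main effect | Label × time | Season of visit (4 levels) |
|---|---|---|---|---|
| May | 1.02, 1.02, −1.02 | 7% | 64% | 82% |
| June | 0.37, 1.40, −0.37 | 15% | 52% | 78% |
| July | −0.38, 1.40, 0.38 | 15% | 52% | 78% |
| August | −1.02, 1.02, 1.02 | 7% | 64% | 82% |

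A mid-June peak gives 17% for the main effect. With splits after 3, 4, 5 or 6 recruitment months and peaks from May to August, the main-effect share stays between about 1% and 17%.

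**Step 4: change from baseline.** The label contributes b − b = 0 to the change from baseline to 3 months. The true seasonal difference in that change between the two label groups is (s₃ − s₀)·A: 0 for a May peak, 1.03A for June, 1.78A for July and 2.04A for August. If two adherence-defined groups differ by a proportion d in their share of later starters, d·(s₃ − s₀)·A stays in their comparison. With d = 0.10 and a July peak, that is 0.18A. Neither d nor A is given, so no figure in minutes can be stated.

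**The case against.** **This is analysis-plan detail in a condensed article.** Exact coding usually is. Here, though, the article names the variable, its levels and the per-protocol model terms, and the point concerns those stated terms. If a fuller plan adds a season-by-time term or visit dates, the main point is answered.

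**Winter starters.** A reader might infer that December–February starters are misclassified, and that 3/8, about 38%, have no valid level. The documents do not support that. The labels may mean an autumn and a spring recruitment wave, monthly accrual is not given, and a January or February start runs partly into spring. Only undefined coding can be claimed.

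**Fit at single visits.** A reader might also infer that the label barely describes baseline and 6 months. That depends on the assumed curve and split. With a December/January split the share is 0–64% at those visits and 64–86% at 3 months. With a November/December split it is 1–82% and 35–83%. The pooled main-effect result stays low throughout.

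**Imputation.** The predictor list is open, and chained equations can give the label a different coefficient at each visit if visits are separate variables. The documents do not show that midwinter and early-summer values are treated as exchangeable. The smaller point that stands is that, under one autumn label, a missing 3-month visit due in December and one due in February are treated alike.

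**Primary result.** Allocation is 1:1 in blocks of two, so the arms stay balanced over calendar time. This objection stands in full.

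**Confounding by adherence is not demonstrated.** That is correct. It is plausible, and the amplitude is unknown.

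**Conclusion.** The point holds for the per-protocol model as written. A per-person season label entered as a main effect cannot adjust change from baseline for season. It captures about 1–17% of an assumed yearly cosine across visits, with visit means removed, for peaks from May to August and splits after 3 to 6 recruitment months. That range assumes even entry and a single yearly cycle. The cancellation from within-person change needs neither assumption. Because adherence is not randomised and may follow the season, this comparison can stay confounded, by an amount the documents do not allow one to calculate. How December–February starts are coded is a secondary gap, and only if calendar seasons are meant. The primary intention-to-treat contrast is not confounded by season, and the effect on imputation is smaller. This is a cheap improvement and does not threaten the trial's main conclusion.

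**What to change.** In the per-protocol model, replace the autumn/spring label with the calendar date of each assessment week, entered per visit as sine and cosine of day of year. Use the same visit date as an imputation predictor, with the scheduled date (randomisation plus 3 or 6 months) for missed visits. That sine and cosine fit the assumed curve fully is true by construction. The fairer comparison is four-level season of the visit, at 78–82% against 7–17% for the label (December/January split).

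If the label is kept, the minimum is to add a season-by-time term and state how December–February starts are coded. At the four tabulated peaks with a December/January split, the interaction raises the share from 7–15% to 52–64%.

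The cost is a change of wording. The assessment weeks supply the dates, and the sample size is unchanged. Sine and cosine use two degrees of freedom where the label uses one.

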### Control group

The control group participants are encouraged to continue with their normal routines and to monitor their daily travels in the TRavelVU app. The app passively collects data on the mode of travel, duration and speed for 6 months, but no behaviour change content is provided. Upon completion of the trial, participants from the control group will have access to TRavelVU Plus, see below, if they wish to.

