### Intervention

#### Overall

The overall aim of the SCAMPI intervention is to increase physical activity levels by promoting active transport. Once allocated to the intervention group, participants receive an email with a user manual for the TRavelVU Plus app. This app differs from the TRavelVU app as it includes a 3-month behaviour change program promoting active transportation. Features of the TRavelVU Plus app (i.e., messages (sent as push notifications), goal setting and feedback functions) are activated and start with a welcome message. The message includes a goalsetting function where participants set their first weekly goal for active transportation, for example 5 h. As guidance, they are informed of the recommendations for adults of 150 min of MVPA per week, but are encouraged to set a goal based on their current activity level. Feedback on the goal is provided in different formats during the week. At the end of the week, participants are able to adjust their goal for the following week. After 3 months, the features of TRavelVU Plus disappear; however, participants are encouraged to keep registering their travels in the TRavelVU app until after the 6-month follow-up assessment.

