##### Behaviour change program (the TRavelVU plus app)

The behaviour change program in the TRavelVU Plus app was developed by Trivector AB © and researchers with experience in behaviour change interventions (obesity, physical activity and transport). The intervention is grounded in Social Cognitive Theory [26] and Social-Ecological [27] principles. To improve the reporting of the content in behaviour change interventions the behaviour change technique taxonomy is recommended [28]. Thus, key behaviour change techniques known to promote physical activity behaviour are included in the app’s features and text messages (e.g., general information about physical activity and active transport, information regarding consequences, barrier identification, specific goal-setting strategies and functions, self-monitoring and feedback on performance) [28]. See Table 1 for theoretical domains, behaviour change techniques and examples of messages. We also considered recommendations from previous research regarding message linguistics (e.g., grammar, spelling, and positivity), dosage, length as well as timing of delivery [29, 30]. Thus, participants receive 4–6 messages per week that contain no more than 200 characters. The program consist of a core set of messages scheduled to be sent at fixed time points throughout the intervention that all participants receive. The messages include practical tips, general information and strategies for behaviour change. The messages can be accessed at any time throughout the intervention and are organised so that the content follow the study timeline. Thus, in the beginning of the intervention messages provide information about features within the app and strategies for goalsetting, and later on the messages focus on past successes and strategies for sustained behaviour changes. The goalsetting feature allows participants to set weekly individual goals for active transportation (i.e., walking and cycling). Feedback is provided in graphical format, where participants can follow their daily and weekly achievements and as a summary of all previous goals (see Fig. 3). During the week a coloured symbol (red, yellow, or green) guides the participants if their present achievement thus far in time spent in active transportation is enough to reach their goal or if greater efforts are needed. Additionally, at the end of each week a feedback message is sent out, which is tailored and varied according to participants’ goals and level of goal achievement in hours and minutes (i.e., ≥100%, ≥70, < 70% or no goal was set).

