#### App usability and quality assessment

To assess the participant’s use of the app we will collect data on the number of registered days (i.e., days the participants marked as valid in the app) for both groups. For the intervention group the number of weekly goals that were set will be assessed and if goals were met, based on the feedback messages delivered. To assess usability and perceived quality of the TRavelVU Plus app, semi-structured interviews will be conducted in a sub-sample of participants who complete the intervention.

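### Goals set and met exist only in the intervention arm, so a between-arm per-protocol comparison built on them can favour the app without a true effect, and the listed covariates cannot be relied on to correct this

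*Protocol article*

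**What the plan says.** Methods, Statistical analyses, evaluates the trial by linear mixed models on intention-to-treat principles. It then adds "Per protocol analyses examining effects related to adherence to the intervention (e.g., number of registered days in the app, goals set and achieved"). These models are to be fitted "adjusting for age, sex, country of birth (Sweden/not Sweden), educational attainment, occupation and season for intervention" and, like the primary model, include time, group and their interaction. Time 0 is the reference level. All p-values below 0.05 two-sided count as significant.

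Other sections fix what the adherence measures are:

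- App usability and quality assessment collects the "number of registered days (i.e., days the participants marked as valid in the app) for both groups". For goals it says: "For the intervention group the number of weekly goals that were set will be assessed and if goals were met".
- Control group says of the control app: "but no behaviour change content is provided". The footnote to Table 1 adds that control feedback is not tied to a goal.
- Behaviour change program describes what a goal is: "The goalsetting feature allows participants to set weekly individual goals for active transportation (i.e., walking and cycling"). The end-of-week message depends on the "level of goal achievement in hours and minutes".
- Intervention, Overall, says participants are "encouraged to set a goal based on their current activity level" and may revise the goal each week.

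**The concern.** Two features set goal achievement apart from ordinary adherence.

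First, it cannot be observed in controls. A criterion that can be applied in only one arm compares a selected part of that arm with an unselected control group.

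Second, meeting a goal means having done the behaviour the trial is trying to increase. For app-measured active transport, a secondary outcome, the criterion and the outcome are the same behaviour from the same data source. For accelerometer MVPA, the primary outcome, the link is indirect, but it is the pathway the trial hypothesises. Because participants are encouraged to set goals from their current activity, achievers are partly selected on having increased.

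The result could be read as showing that the app works in people who use it. The Discussion itself foresees a diluted or reduced effect, from self-monitoring in controls and from recruiting people who are already active. A null intention-to-treat result beside a favourable per-protocol one is therefore a realistic outcome to plan for.

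**Working it through.** **1. The plan's own figures.** Sample size and power considerations gives a difference of 10 min/day, SD 25, two-sided 0.05 and 80% power.

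n per arm = 2 × (1.960 + 0.842)² × 25² / 10² = 98.1, so 99. Power at 100 per arm is 0.807 (normal) or 0.804 (t). Enrolment is 200 / 0.80 = 250. All of this reproduces. The 10 min/day and SD 25 serve as the yardstick below.

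**2. Which measures can be applied in which arm.**

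| Measure | Intervention | Control | Relation to outcome |
|---|---|---|---|
| Registered days | yes | yes | app use |
| Goals set | yes | not possible | app use |
| Goals achieved | yes | not possible | same as app-measured active transport; indirect for MVPA |

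If goal achievement defines a subset, achievers face all controls. If it enters as a model term, it is zero by construction in every control and conditions on post-randomisation behaviour. Neither use is protected by randomisation.

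**3. Size with no true effect.** Assumptions not in the document: 100 completers per arm before selection, the better half of the intervention arm kept, within-person correlation 0.6, and correlation r between achievement and MVPA change.

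- SD of change = 25 × √(2 × (1 − 0.6)) = 22.4.
- Spurious difference in change = r × 22.4 × φ(0) / 0.5 = r × 22.4 × 0.798 = 17.8 r.
- SE = √(22.4² × (1 − 0.637 r²) / 50 + 22.4² / 100), where 0.637 = 0.798².

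| r | Spurious benefit (min/day) | SE | Chance of p < 0.05 in favour of the app |
|---|---|---|---|
| 0 | 0 | 3.9 | 2.5% |
| 0.3 | 5.4 | 3.8 | 29% |
| 0.4 | 7.1 | 3.7 | 48% |
| 0.5 | 8.9 | 3.7 | 68% |

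Simulation agreed: 5.4 and 9.0 min/day at r = 0.3 and 0.5. The fitted mixed model at r = 0.5 rejected in favour of the app in about 69% of trials, or 60% with 20% of visits missing.

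If achievement instead tracks the level of MVPA at 3 months, the difference in change is r × 25 × 0.798 × (1 − 0.6) = 8.0 r, or 2.4 to 4.0 min/day for r from 0.3 to 0.5.

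**4. What the covariates do.** Write the model as Y(i,t) = time(t) + group + group × time(t) + γX(i) + person effect + error. In the change Y(i,3) − Y(i,0), the term γX(i) cancels. With complete data, a time-constant main effect therefore leaves the group-by-time estimate unchanged. Simulated at r = 0.5: 8.72 unadjusted and 8.72 adjusted. Other specifications, also at r = 0.5 with goals relative to own baseline:

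| Specification | Unadjusted | Adjusted |
|---|---|---|
| Main effects, 20% of visits missing | 8.88 | 8.83 |
| Covariate × time | 8.9 | 8.2 |
| Difference in level at 3 months | 5.6 | 3.5 |
| Baseline-adjusted ANCOVA | 8.1 | 5.9 |

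The last three rows assume covariates that explain 20% of the visit-level variation at follow-up. Across all runs the largest reduction was a little under half with goals relative to own baseline (3.84 to 2.07, level contrast), and about three fifths when achievement tracked level (8.05 to 3.13). A positive bias remained in every goal-achievement run with r above zero.

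**The case against.** The strongest reply is that the article fixes less than the concern needs. The adherence measures are examples, with no threshold, and the text does not say whether they define a subset or enter the model as a term. That detail often sits in an analysis plan that is not shown. This stands as a limit on the size. It does not remove the point, because goals set and met are expressly among the examples and the model expressly contains group terms.

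Three stronger readings are tempting, and the document does not support them.

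- *The adjustment has no effect on the estimate.* This is exact only for the group-by-time coefficient with complete data and time-constant main effects. The planned multiple imputation would supply complete data sets, but the article does not say how the covariates enter. A footnote to Table 2 also shows that occupational status is collected again at follow-up. Nor does the article present the covariates as a cure for selection.
- *The analysis would show a benefit whatever the app does.* That depends on r, for which the document gives no value. Goals are self-set and adjustable, so meeting one may reflect an easy target, and the link to accelerometer MVPA is indirect. Registered days exist in both arms and need not create this bias.
- *The trial's main conclusion is compromised.* Nothing gives the per-protocol result priority over intention to treat.

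**Conclusion.** The point holds as a moderate one. A between-arm contrast built on goals set or achieved is not protected by randomisation. Where achievement decides who is compared, the contrast can be expected to favour the app under no true effect, to the extent that achievement tracks change in MVPA. Under the stated assumptions this is about 5 to 9 min/day against a planned effect of 10. It is smaller if achievement tracks activity level rather than change, and about 0 at zero correlation. The listed covariates cannot be relied on to remove it. The primary intention-to-treat analysis is unaffected.

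**What to change.** In Statistical analyses:

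1. Remove goals set and goals achieved as criteria for any between-arm per-protocol comparison.
2. Report both within the intervention arm only, descriptively or as associations.
3. Base any between-arm adherence analysis on a measure collected in both arms. Registered days, applied by the same rule to each arm, is available.
4. Label that analysis exploratory and not protected by randomisation.

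Registered days are not free of selection either. In runs where retention in the intervention arm followed a stable personal trait, the bias in change was about 0 when covariates did not predict change. A difference in level of 4.5 to 7.8 min/day remained before adjustment in those runs with r from 0.3 to 0.5. Hence the exploratory label.

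A complier-average analysis with weeks of goal setting as the exposure is not a ready substitute. Every intervention participant receives the core messages whether or not a goal is set, so assignment can affect MVPA by another route and the exclusion restriction is implausible.

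The cost is wording, plus giving up a between-arm estimate among goal achievers.
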